### Study population, recruitment, and retention

#### Sampling and recruitment

##### Schools

The study involves the active collaboration of the Masaka Diocese which operates slightly over 420 public primary schools in Rakai District and the greater Masaka region. We will recruit medium-sized schools to participate in the study. All schools with a total enrollment of more than 900 students will be eliminated as they are considered above average enrollment. Similarly, all schools with a total enrollment of less than 350 students will be dropped because they are considered below the average normal enrollment of at least 50 students per grade. Schools that remain on the list after this stratification will be contacted to schedule informational meetings with the school leadership and staff (school heads/directors, head teachers, and teachers) to present the research study and gauge interest in study participation. Follow-up meetings will be scheduled when necessary. The research team will compile a list of the schools that express commitment to participating in the study (see the “Randomization” section for further details).

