### Randomization

Stratified cluster randomization of schools to conditions will be used, with schools stratified into four strata based on two variables: (1) student population size (medium size vs. large) and; (2) geographical location (rural vs. semi-urban), to ensure balance on those variables. The restricted randomization technique of Hayes and Moulton [99] will be used to assure overall school balance across the three experimental groups. Each school will be randomly assigned to one of the three study conditions such that all selected children from a particular school will receive the same intervention (reduce contamination). These schools are geographically apart, with limited transportation. Hence, the risk for contamination will be minimal (See the “Contamination” section).

Specifically, to select and randomize the potential schools, we will follow the following procedure:A list of the primary schools in the area will be obtained from the Masaka Diocese that oversees all the 420 church-founded but government-supported public primary schools in the Rakai District and Masaka regions; and the District Education OfficeAll schools with a total enrollment of more than 900 students will be eliminated as they are considered above average enrollment. Similarly, all schools with a total enrollment of less than 350 students will be dropped because they are considered below the average normal enrollment of at least 50 students per gradeSchools that remain on the list after this stratification will be contacted to schedule informational meetings with the school leadership and staff (school head teachers, and teachers) to present the research study and gauge interest in the study. During these meetings, the purpose of the study will be explained and what the school’s participation entails will be laid out. All study-related questions will be answered. Follow-up meetings will be scheduled when necessaryThe research team will compile a list of the schools that express commitment to participating in the studyThirty schools from this list will be randomly chosenUsing SPSS software version 24, each of these 30 schools will be randomly assigned to one of the three study conditions, i.e., 10 to the adapted MFG delivered by parent peers; 10 to the adapted MFG delivered by CHWs; and 10 to the comparison condition

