#### Quantitative data management and analyses

*Exploratory scale structure analysis*. The research will use robust estimators (in the form of Huber-White estimation) to accommodate non-normality and variance heterogeneity. We will conduct formal tests of outliers and be sensitive to specification error. Inter-item reliability analyses for all scales will be conducted using confirmatory factor analytic (CFA) perspectives; correlations across time and construct will be examined*Data-reduction procedures*. Most of the proposed instruments have summary scoring procedures; however, multiple scores in specific domains may result in multicollinearity, requiring further data reduction. Various data-reduction strategies will be conducted, including factor analyses with oblique rotation [113] and Chi-squared Automatic Interaction Detector (CHAID) algorithms, to identify the strongest variables in the pool. The Exhaustive CHAID method, developed by Biggs, deVille and Suen [114] will be used to explore various groups of predictor variables as they relate to outcomes*Tests of sample equivalence across study conditions*. We will use baseline data to examine potential biases related to possible attrition by condition or selection biases not addressed by random assignment. Preliminary analyses will be performed to compare the schools, facilitators, and adult caregivers in the three study conditions on descriptive/clinical characteristics at baseline to ensure that randomization succeeded. Any ancillary variables that are not the focus of hypotheses, but relate meaningfully to outcomes within treatment groups are candidates for inclusion as covariates. When covariates differentiate treatment groups, they will be included in all analyses to remove confounding effects*General statistical considerations*. To address *aims # 1 and 2*, we will use random-effects models to examine scores over the four assessments. Random-effects models have characteristics that provide solutions to commonly observed problems in the analysis of longitudinal data; missing data, serial correlation, and time-varying covariates [114]. These analyses can model systematic person-specific deviations from the average time trend. Just as the nesting of participants within providers is an example of multi-level data, the nesting of perspectives within teacher reports can also be viewed as multi-level data. By treating treatment perspective as a “repeated measurement” we can estimate the difference between the three conditions on outcomes as a synthesis of the three perspectives. Divergence between the perspectives can also be examined by including interactions between covariates, condition and the rater effect. We will model each outcome as a function of group, time and group-by-time interaction. We will use Supermix software for the mixed-effects linear regression [96].To address aim 3, our analyses will use variants of structural equation modeling (SEM) with Mplus. The models we test often will be statistically over-identified. We will evaluate model fit using both global fit indices (e.g., relative/normed chi-square *χ*^2^/df with range 2.0–5.0) [115, 116], comparative fit index (CFI) (with value ≥ 0.95) [117], standardized root mean square residual (RMR (below 0.08) [117], root mean square error of approximation (RMSEA) (with the lower limit is close to 0 and the upper limit less than 0.07) [118] and indices of fit that are diagnostic of specific points of ill fit in the model (e.g., standardized residuals, modification indices). If poor model fit, then we will examine diagnostics that suggest revisions to the model that are meaningful and that will significantly improve model fit.Hypotheses testing

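### Covariates enter every model according to observed baseline differences between arms, the stated model names no stratification factor, and the size stratum conflicts with the school enrolment limits

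*Protocol article*

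**What the plan says.** **Adjustment rule** (Protocol article, Quantitative data management and analyses, item on sample equivalence). Schools, facilitators and caregivers are compared across the three conditions "at baseline to ensure that randomization succeeded". Ancillary variables that "relate meaningfully to outcomes within treatment groups are candidates for inclusion as covariates". Then: "When covariates differentiate treatment groups, they will be included in all analyses to remove confounding effects". No variables are listed, and no threshold is given for being meaningfully related or for differentiating the arms.

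**Outcome model** (same section). "We will model each outcome as a function of group, time and group-by-time interaction". For Aims 1 and 2, "we will use random-effects models to examine scores over the four assessments". The Aim 1 section makes the condition-by-trajectory interaction the effect of primary interest and says only that school dummy codes may be added. No stratification factor is named.

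**Strata and eligibility.** The Randomization section has "schools stratified into four strata based on two variables: (1) student population size (medium size vs. large" and, second, rural or semi-urban location. The Schools section says medium-sized schools will be recruited, and that "All schools with a total enrollment of more than 900 students will be eliminated as they are considered above average enrollment". Schools below 350 students are dropped too. The stepwise list under Randomization repeats both limits and then assigns 30 schools, 10 per condition, in SPSS without mentioning strata.

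**The concern.** Under randomisation, a baseline difference between arms is a chance event, apart from faults in conduct. A rule that turns such differences into model terms lets chance choose the primary model. The outcome screen does not cure this: relating a variable to outcome within treatment groups appears to need the trial's own outcome data, so it is a second data-dependent step.

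Meanwhile the variables that design gives a reason to adjust for, the factors used to balance the allocation, are not named. When randomisation is balanced on a factor related to outcome and the analysis ignores it, the estimated standard error is too large: the test becomes conservative and precision is lost.

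The size factor also has to be definable before it can balance the allocation or enter a model. As written, its upper category appears to be the group that eligibility removes.

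**Working it through.** The article gives no figure for this point to reproduce. The calculations below are illustrations, with assumptions marked.

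**1. How often chance would decide the covariate set.** Let k be the number of candidates that passed the outcome screen (assumed), each compared across arms by an independent valid test at 5% (assumed). Then P(at least one flagged) = 1 − 0.95^k.

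| k | P(at least one flagged) |
|---|---|
| 5 | 23% |
| 10 | 40% |
| 14 | 51% |
| 20 | 64% |

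**2. If the baseline comparisons ignored clustering** (the article does not say). Statistical power calculations sets the effective sample size at two thirds of the actual one, so the design effect is 1/(2/3) = 1.5. With 3000/30 = 100 children per school this implies an ICC of (1.5 − 1)/(100 − 1) ≈ 0.005. A three-arm test (2 df, critical value 5.99) then has a false-positive rate of P(χ² > 5.99/1.5) = exp(−5.99/3) ≈ 0.136. For 10 variables, 1 − (1 − 0.136)^10 ≈ 77%. At an assumed ICC of 0.02 the design effect is 1 + 99 × 0.02 = 2.98 and the per-test rate is 37%; at 0.05 it is 5.95 and 60%.

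**3. Effect of omitting the strata.** Let R² be the share of the error variance of the tested school-level contrast that the strata explain (assumed). The standard error is overstated by s = 1/√(1 − R²). In a normal approximation, type I error is 2(1 − Φ(1.96s)), and a test with 80% power when adjusted (2.80 standard errors) has power Φ(2.80 − 1.96s).

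| R² | s | Type I error | Power |
|---|---|---|---|
| 0 | 1 | 5% | 80% |
| 10% | 1.054 | 3.9% | 77% |
| 20% | 1.118 | 2.8% | 73% |
| 30% | 1.195 | 1.9% | 68% |
| 50% | 1.414 | 0.6% | 51% |

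For this trial, R² must refer to school trajectories, because the primary effect is group-by-time. A constant rural versus semi-urban difference in level largely cancels from change over time. The article gives nothing from which R² could be taken, so the table shows direction and range and is not an estimate.

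**4. Direction check by simulation.** School means were simulated under no effect: 30 schools, 10 per arm, randomised within two strata, 6000 runs. Assumed values were a stratum difference of 0.8, baseline coefficient 0.6, one further prognostic covariate 0.3, and residual SD 0.6.

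| Model | Type I error | Mean SE | Empirical SD |
|---|---|---|---|
| Unadjusted | 0.029 | 0.440 | 0.399 |
| Covariates chosen by imbalance | 0.022 | 0.446 | 0.391 |
| Prespecified strata plus baseline | 0.051 | 0.302 | 0.304 |

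The first two models overstate the standard error; the third does not. This is a single-endpoint analysis, so the part of the gain due to baseline does not carry over to the article's repeated-measures model, which already contains baseline.

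**5. Size stratum, sections side by side.** Randomization needs two size categories, medium and large. Schools admits only medium-sized schools, and both sections keep only those with 350 to 900 students. If large means above 900, the large strata are empty and the four strata collapse to two. If large means the upper part of 350 to 900, the cut is not stated.

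**The case against.** - **Imbalance is not the only criterion.** True: candidates must first be related to outcome within arms. This makes the rule less arbitrary and means that the percentages in steps 1 and 2 apply only to variables that passed that screen. It does not make the covariate set prespecified.
- **The missing strata may be in the analysis plan.** Fair. Silence on stratum terms in a condensed article is not an error in itself, and nothing rules them out. The point rests on the rule that is stated, which commits all analyses to data-selected covariates.
- **A reader might infer that the baseline outcome is left out of the model.** The article does not support this. Its Methods section lists baseline among the four assessments, and the primary effect is divergence over time. Table 3 lists the Iowa scale at screening and not at T1, so the screening score can serve as its baseline.
- **A reader might infer that the type I error is inflated.** The cases computed show the opposite, a conservative test.
- **A reader might infer that the large strata are proven empty, or that allocation was unstratified.** Neither is shown. Large has no stated cut-off, and the Randomization section opens with stratified cluster randomisation and restricted randomisation before giving the list. What stands is that the term is undefined and conflicts with the recruitment wording.

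**Conclusion.** The point holds in two parts.

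1. The article states a data-dependent adjustment rule that reaches every analysis, including the primary condition-by-trajectory test, while naming none of the design factors. The probability that chance alone adds a covariate is substantial over any plausible number of candidates (23% for 5, 64% for 20, under independence and a 5% threshold, both assumed). Leaving out prognostic strata costs precision and makes the test conservative only so far as strata explain differences in school trajectories; that size cannot be derived from the article and could be small.
2. The medium versus large stratum does not agree with the recruitment and enrolment limits, and the passages must be reconciled. Empty strata are the natural reading but not a proven one.

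This should be changed. It does not show that the trial's conclusions would be anti-conservative.

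**What to change.** - Replace the imbalance rule with a prespecified covariate set for the Aim 1 models: the reconciled size and location strata, with stratum-by-time terms where the test is group-by-time, plus named prognostic variables such as child age and sex.
- Keep baseline as one of the repeated responses and do not add it again as a covariate.
- For Aim 2 use only the strata. Fidelity is recorded at sessions, with no pre-intervention value and no child-level age or sex.
- Report baseline balance descriptively and do not let it drive adjustment.
- Define the size stratum by an enrolment cut inside 350 to 900, for example the median of the 30 schools, or drop the factor. Have the stepwise list say that allocation is done within strata.
- If schools are already allocated, which is possible because the Trial status section reports recruitment and baseline assessment under way, document the strata actually used and analyse by those.

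**Cost:** wording, and a few school-level degrees of freedom. With 30 schools and 3 arms, 30 − 3 = 27 remain between schools; two additive stratum terms leave 25, and coding all four strata (three terms) leaves 24. Stratum-by-time terms take a similar number from the trajectory comparison.

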**Methods:**

The MFG intervention will be implemented and tested via a longitudinal experimental study conducted across 30 public primary schools located in both semi-urban and rural communities. The schools will be randomly assigned to three study conditions (*n* = 10 per study condition): (1) MFG delivered by trained family peers; (2) MFG delivered by community health workers; or; (3) comparison: usual care comprising mental health care support materials, bolstered with school support materials. A total of 3000 children (ages 8 to 13 years; grades 2 to 7) and their caregivers (*N* = 3000 dyads); 60 parent peers, and 60 community health workers will be recruited. Each study condition will comprise of 1000 child-caregiver dyads. Data will be collected at baseline, 8 and 16 weeks, and 6-month follow-up.

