##### Children and caregivers

Schools will be asked to organize meetings for all families to learn about the study. All research staff will be on hand at each meeting to provide the opportunity for parents to ask questions about the study individually or as part of a larger group of parents. If parents and children are interested in participating, each of them will have an opportunity to meet individually with research staff and provide informed consent and child assent.

Following consent procedures, parents will be asked to complete screening tools for child DBDs (see Table 3). The screening will be conducted by project coordinators and research assistants. If the child meets the criteria for a clinically meaningful behavioral problem on any of the screening measures, they will be considered “positive”. They and their caregivers will be invited to enroll in the study and an appointment to complete a full baseline assessment (for both child and caregiver; see the “Measures” section) will be made prior to beginning to attend MFG meetings. If a child does not evidence a DBD, they will be considered “negative.” The family will be enrolled to attend the MFG meetings (all families in the school community will have the opportunity to attend to decrease stigma, but also enhance functioning of all parents/families). An appointment to complete a shortened version of the baseline assessment (for both child and caregiver; see the “Measures” section) will be made prior to beginning to attend MFG meetings. The child and the caregiver will be monitored at each time point with shortened versions of the assessment batteries. If at any point during these assessments, the child meets criteria for DBD, both the child and the caregiver will complete full version of the assessment batteries.

School meetings is the first way that we will reach out to parents of children enrolled in the potential schools. Research staff will also conduct home visits (as has been typically done in other studies in the area). In total, we will recruit 3000 children and their adult caregivers across three study conditions. We will continuously monitor study participants’ recruitment and enrollment during weekly staff meetings to ensure equivalent involvement across conditions by: gender of youth, age and adjust if imbalance occurs accordingly.

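### The Aim 3 normed chi-square criterion of 2.0–5.0 is mis-stated: as an interval it excludes nearly all correct models, and as an upper cut-off it is much stricter than the RMSEA limit beside it

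*Protocol article*

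**What the plan says.** The protocol article, under Quantitative data management and analyses (general statistical considerations), assigns Aim 3 to structural equation modelling and notes: "The models we test often will be statistically over-identified". Fit is to be assessed as follows: "We will evaluate model fit using both global fit indices (e.g., relative/normed chi-square", with the criterion for that ratio given as "df with range 2.0–5.0) [115, 116], comparative fit index (CFI) (with value ≥ 0.95". The standardized RMR is to lie below 0.08. The RMSEA condition is worded "with the lower limit is close to 0 and the upper limit less than 0.07". Local diagnostics, including standardized residuals and modification indices, are listed alongside the global indices.

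The consequence of a bad result is then stated: "If poor model fit, then we will examine diagnostics that suggest revisions to the model that are meaningful and that will significantly improve model fit".

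The CFI and RMR cut-offs are one-sided. Only the normed chi-square has a lower end above its ideal value. The article does not say that a ratio below 2.0 is poor fit, how the indices are combined, or which one governs when they disagree.

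**The concern.** A fit criterion should let well-fitting models through. Chi-square/df averages 1 when the model is correct, so a band starting at 2.0 admits only models that show some misfit or are unlucky. The natural rescue is to read 2.0 and 5.0 as alternative upper cut-offs. That does not settle the matter, because chi-square/df grows with sample size for a fixed degree of misfit and RMSEA does not. In a trial of this size the two criteria set very different standards.

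At stake are the Aim 3 conclusions about school, facilitator and family paths. A poor-fit verdict opens a search for revisions in the same data. Path tests from a model revised that way capitalise on chance, and their p-values tend to be too small. Where the indices disagree, choosing which one to follow after seeing the results is a further analytic freedom.

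**Working it through.** The 2.0–5.0 range is a cited threshold, not a figure derived from trial inputs, so there is nothing to reproduce. The check is what it implies here.

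**Inputs from the article**
- Total families (Children and caregivers): "In total, we will recruit 3000 children and their adult caregivers across three study conditions".
- Per arm (Abstract, Methods): "Each study condition will comprise of 1000 child-caregiver dyads". The two MFG arms together give 2000.
- Attrition of at most 20% (Sample attrition and retention): 3000 × 0.80 = 2400. With 8% per interval over three intervals (Statistical power calculations): 3000 × 0.92³ = 2336.
- Effective sample size of two thirds (Statistical power calculations): 3000 × 2/3 = 2000.

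**Assumptions.** Neither the models' df nor the Aim 3 analysis N is given, so ranges are shown. The RMSEA identity is the single-level one.

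**Step 1: interval reading, correct model.** Here chi-square/df has mean 1, and the probabilities come from the central chi-square distribution. This step does not depend on N.

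| df | P(ratio < 2) | P(2 ≤ ratio ≤ 5) |
|---|---|---|
| 1 | 84.3% | 13.2% |
| 5 | 92.5% | 7.5% |
| 10 | 97.1% | 2.9% |
| 20 | 99.5% | 0.5% |
| 50 | 99.997% | 0.003% |

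**Step 2: upper cut-off reading against RMSEA.** RMSEA = √[(ratio − 1)/(N − 1)], so ratio = 1 + (N − 1) × RMSEA². For example, at N = 3000 a ratio of 5 gives √(4/2999) = 0.0365, and RMSEA 0.07 gives 1 + 2999 × 0.0049 = 15.7.

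| N | RMSEA at ratio 2 | RMSEA at ratio 5 | Ratio at RMSEA 0.07 |
|---|---|---|---|
| 3000 | 0.018 | 0.037 | 15.7 |
| 2400 | 0.020 | 0.041 | 12.8 |
| 2336 | 0.021 | 0.041 | 12.4 |
| 2000 | 0.022 | 0.045 | 10.8 |
| 1600 (two arms, 20% lost) | 0.025 | 0.050 | 8.8 |

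A ratio of 5 coincides with RMSEA 0.07 at N = 1 + 4/0.0049 ≈ 817, and a ratio of 2 does so at N = 1 + 1/0.0049 ≈ 205. Both lie well below the planned number of families.

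**Step 3: where the verdicts differ (N = 2000 to 3000, RMSEA as a point limit).**
- Ratio below 2: passes RMSEA, lies outside the printed range.
- Ratio 2 to 5: passes both (RMSEA about 0.018 to 0.045).
- Ratio 5 to about 11–16: passes RMSEA, fails a cut-off of 5.

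Example: RMSEA 0.055 gives a ratio of 1 + 1999 × 0.003025 = 7.0 at N = 2000 and 1 + 2999 × 0.003025 = 10.1 at N = 3000. With df 40 the upper 90% limit is 0.061 and 0.060 respectively, inside 0.07.

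**Step 4: RMSEA limits read as a 90% interval.** At N = 3000 and df 50, a ratio of 1 gives (0, 0.012), 2 gives (0.013, 0.023) and 5 gives (0.032, 0.041). A lower limit near zero thus favours ratios under 2, the region the printed floor leaves out. How near is near enough is not defined, and a strict reading would shrink the disagreement above 5.

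**The case against.** A reader might infer that the plan scores a correct model as poor fit. It does not say so. The indices are introduced as examples, no single one is made decisive, and a value below 2.0 is never called poor. The range carries two citations and may be meant as a span of published upper cut-offs. That objection stands: the wording is ambiguous, not an explicit rule that rejects correct models.

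A reader might also infer that the chi-square and RMSEA criteria contradict each other. With 2000 to 3000 families they do not: every ratio from 2 to 5 meets the 0.07 point limit. They differ in strictness, and several indices are usually listed because they do not always agree.

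Nor is respecification automatic. Revisions must be meaningful and must improve fit significantly, and a correct model should show few large modification indices. How often a correct model would be altered, or p-values distorted, has not been estimated.

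The figures in Step 2 do not cover all of Aim 3 either. The plan uses three-level models and robust estimation, which would change the exact values. It also allows sub-models for facilitator and school variables. With 120 facilitators as the units, a ratio of 2 would be RMSEA √(1/119) = 0.092, so the order of strictness reverses.

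These points limit the consequence. They do not repair the sentence: one reading has a floor in the wrong place, and the other leaves open which cut-off applies and ties it to sample size.

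**Conclusion.** The point holds in a limited form. The criterion is mis-stated on either reading. As an interval it leaves out about 97% of correct models at df 10 and 99.5% at df 20. As an upper limit of 5 it demands an RMSEA of about 0.037 to 0.045 at 3000 to 2000 families, against the stated 0.07. It can add weight to a poor-fit verdict and so to revision on the same data, but it compels neither.

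Step 1 rests on assumed df. Step 2 also rests on the assumed analysis N and the single-level identity. The effect is confined to Aim 3 model evaluation; the Aim 1 group-by-time test uses mixed models and is untouched. Severity is minor to moderate, with moderate confidence.

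**What to change.** Remove the lower bound and report chi-square/df as descriptive only, stating that it does not prompt revision, or drop it. Judge global fit on the CFI, standardized RMR and RMSEA limits already in the text. Report the pre-specified Fig. 1 model in every case, and label any model revised from modification indices as exploratory.

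This costs about one sentence of analysis wording and, where a model is revised, one extra set of results. Design, sample size and data collection do not change.
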